#### Oral glucose tolerance test

2.11.3

Venous fasting blood samples will be collected the following morning to avoid prolonged fasting that could lead to reactive hyperglycemia and interfere with diagnostic accuracy. A glucose solution will be prepared by dissolving 75 g of anhydrous glucose powder in 150 mL of water, and participants will be instructed to consume the entire 150 mL solution within 5 minutes. The start of ingestion will be recorded as time zero. Venous blood samples will then be collected at fasting, 60 and 120 minutes after ingestion to assess blood glucose changes.

#### Lipid metabolism

2.11.4

Lipid metabolism parameters, including high-density lipoprotein cholesterol (HDL-C), low-density lipoprotein cholesterol (LDL-C), triglycerides (TG), and total cholesterol (TC), will be measured using a fully automated biochemical analyzer. Blood collection and storage will follow the standard protocol described above, and lipid profiles will be assessed using corresponding assay kits.

#### Energy metabolism

2.11.5

One hour after consuming a standardized meal, participants will undergo a 30-minute resting respiratory exchange ratio (RER) test using a metabolic gas analyzer (Cortex Meta Max 3B, CORTEX, Germany) while lying supine. The mean RER will be calculated after excluding data from the first and last 5 minutes. Subsequently, participants will perform 30 minutes of AE at 60% of their individual VO_2_peak to measure exercise RER. During the test, workload will be adjusted based on oxygen consumption to ensure the target intensity is maintained. Metabolic flexibility will be evaluated using the difference between exercise and resting RER (
ΔRER=RER_exercise−RER_rest), with a larger ΔRER indicating greater metabolic flexibility.

#### Cardiovascular risk factors

2.11.6

Height, body weight, waist circumference, and hip circumference will be measured using a stadiometer, digital scale, and non-elastic measuring tape to assess cardiovascular risk factors. Body mass index will be calculated as 
$\;\text{body weight (kg)}/\text{height squared (}{\text{m}}^{2})$. Waist-to-hip ratio (WHR) will be calculated as
 waist circumference (cm)/hip circumference (cm). Subcutaneous adipose tissue thickness will be measured at three sites—triceps, subscapular, and abdominal regions—using a skinfold caliper. In addition, an ultrasound body composition analyzer (BodyMetrix BX-2000, Intelametrix, Livermore, USA) will be used to assess fat thickness at seven anatomical sites, including the triceps, subscapular, mid-axillary, abdominal, pectoral, suprailiac, and thigh regions.

#### Echocardiography

2.11.7

After resting in the supine position for 5 minutes, participants’ right brachial artery blood pressure will be measured three times and recorded. Participants will then be placed in the left lateral decubitus position, connected to an ECG, and examined using a GE Vivid E95 color Doppler ultrasound system equipped with an M5S transducer. Dynamic images from three consecutive cardiac cycles will be acquired and stored from the following standard echocardiographic views: parasternal long-axis view of the left ventricle, parasternal short-axis views at the basal, mid-papillary, and apical levels, and apical four-chamber, two-chamber, and three-chamber views.

Cardiac Structural and Systolic Function Parameters: From the parasternal long-axis view, left ventricular end-diastolic diameter (LVEDD), end-systolic diameter (LVESD), interventricular septal thickness (IVST), and left ventricular posterior wall thickness (LVPWT) will be measured. Left ventricular remodeling indices—including relative wall thickness (RWT) and left ventricular mass index (LVMI)—will be calculated. Systolic function parameters, including left ventricular ejection fraction (LVEF), stroke volume (SV), and cardiac output (CO), will be obtained using the biplane Simpson’s method from the apical four-chamber and two-chamber views.

Diastolic Function Parameters: Pulsed-wave Doppler (PW) will be used at the mitral valve inflow to measure early (E) and late (A) diastolic filling velocities. Tissue Doppler imaging (TDI) will be applied at the septal and lateral mitral annulus to measure early diastolic myocardial velocity (e’), from which the mean e’ and mean E/e’ ratio will be calculated to evaluate left ventricular diastolic function.

#### Electrocardiography

2.11.8

A standard 12-lead resting electrocardiogram (ECG) will be recorded using a digital ECG system (EDAN SE-1010, China) after the participant has rested in a supine position for at least 10 minutes. All intervals will be measured from lead II, except for the QT interval, which will be measured in either lead II or V5 (whichever is clearer). The following parameters will be analyzed: P-wave duration (ms), PR interval (ms), QRS duration (ms), and QT interval (ms). The QT interval will be corrected for heart rate (QTc) using Bazett’s formula:

$$\text{QTc}=\text{QT}/\sqrt{\text{RR}}.$$

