### Research setting

2.2

A total of 74 participants with T2DM will be recruited from local communities in Shenyang, China in collaboration with community physicians. Recruitment strategies will include the distribution of posters, flyers, brochures, and health education lectures. Clinical physicians will confirm the diagnosis and assess eligibility for all potential participants. The exercise intervention will be conducted at a fitness and rehabilitation center, while all clinical assessments will take place at a partner hospital and associated laboratories. Baseline and follow-up assessments will be conducted by trained research staff who are blinded to group allocation, and the exercise intervention will be supervised by certified clinical exercise physiologists. Participant recruitment commenced in June 2025. The study execution period is from June 30, 2025, and is currently ongoing (**Figure 1**).

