### Measurement

2.8

Comprehensive clinical assessments—including metabolic, cardiovascular, cardiopulmonary, fatigue, and skeletal muscle tests—will be performed at baseline and at the 12-week follow-up. With the exception of the oral glucose tolerance test and associated 2-hour postprandial glucose measurement, all assessments will be conducted in the morning after a minimum 12-hour overnight fast. Participants will be instructed to abstain from alcohol, caffeine for 24 hours and withhold their morning medications on the day of assessment to minimize pharmacological interference. To mitigate the confounding effects of acute exercise, post-intervention assessments will be scheduled 48 hours after the final training session. For biochemical analyses, venous blood samples (approximately 6 mL) will be drawn from an antecubital vein into serum separation tubes. The tubes will be gently inverted and then allowed to clot at room temperature for 30–60 minutes. The samples will then be centrifuged at 3000 rpm for 10 minutes at 4°C, and the resulting serum will be aliquoted and stored at –80°C until analysis. To minimize inter-assessor and instrument variability, all measurements will be performed by the same trained technician using the same equipment at both time points.

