### Statistical analysis

2.12

All statistical analyses will be performed using R software (version 4.3.1 or later; R Foundation for Statistical Computing, Vienna, Austria). For the description of baseline data, normally distributed continuous variables will be presented as 
mean±standard deviation (SD), while non-normally distributed variables will be reported as median [interquartile range (IQR)]; categorical variables will be expressed as frequencies and percentages (n, %). For the comparison of baseline data between groups, independent samples t-tests will be used for normally distributed continuous variables, the Mann-Whitney U test will be used for non-normally distributed data, and the chi-square (χ²) test or Fisher’s exact test will be used for categorical data.

Efficacy analyses will be conducted according to the intention-to-treat (ITT) principle and will include all randomized participants. Continuous outcomes, including NMD and GWE, will be analyzed using linear mixed-effects models (LMMs). To rigorously control for potential confounding, background medication use will be prespecified and included as fixed-effect covariates in the models. Medications will be categorized by therapeutic class, with binary indicators (yes/no) created for: (1) glucose-lowering agents (with separate indicators for GLP-1 receptor agonists and SGLT2 inhibitors), (2) antihypertensive medications, and (3) statins. Each LMM will incorporate group, time, and the 
group×time  interaction as fixed effects, with a random intercept for each participant to account for repeated measurements.

Sensitivity analyses will be performed using multiple imputation to assess the robustness of the findings under different assumptions regarding missing data. In addition, a per-protocol (PP) analysis will be conducted as a secondary sensitivity analysis, including only participants with an attendance rate of at least 80%. Secondary outcomes will be considered exploratory and hypothesis-generating; therefore, no adjustment for multiple comparisons will be applied. A two–tailed *P*–value < 0.05 will be considered statistically significant.

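### QT may be read in lead II or V5 by clarity, with nothing tying the lead across the two visits, so a change of lead can add avoidable noise to the QT and QTc change

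*Protocol article*

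**What the plan says.** Section 2.11.8 (Electrocardiography) specifies a resting 12-lead ECG and sets the lead for each interval: "All intervals will be measured from lead II, except for the QT interval". For that one interval the text leaves a choice of two leads, decided by clarity: "which will be measured in either lead II or V5 (whichever is clearer". QTc is then derived from that same reading: "The QT interval will be corrected for heart rate (QTc) using Bazett’s formula".

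Section 2.8 (Measurement) says that the clinical assessments "will be performed at baseline and at the 12-week follow-up". Its rule for consistency between visits is that "all measurements will be performed by the same trained technician using the same equipment at both time points". The ECG lead is not mentioned there.

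Section 2.12 (Statistical analysis) models continuous outcomes with group, time and their interaction, medication covariates, and a model structure "with a random intercept for each participant to account for repeated measurements". No term for ECG lead is listed. The same section says: "Secondary outcomes will be considered exploratory and hypothesis-generating".

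Section 2.2 (Research setting) assigns the baseline and follow-up assessments to "trained research staff who are blinded to group allocation".

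**The concern.** What matters for QT and QTc is the change within a participant between two ECGs. QT measured in one lead need not equal QT measured in another on the same tracing. If the lead stays the same, a stable lead difference is present at both visits and cancels from the change. If the lead moves from II to V5, or the reverse, the recorded change is the true change plus or minus the lead difference.

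The written rule selects by clarity, which is a property of a tracing, and it does not link the two selections. A technician could read II at baseline and V5 at week 12 and comply fully with sections 2.8 and 2.11.8. What is at stake is precision of the QT and QTc change and the trustworthiness of an individual participant's change, not the trial's main conclusions.

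**Working it through.** **What the rules allow.** Three passages bear on the question.

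- Section 2.11.8: lead chosen by clarity between II and V5; no statement on carrying the choice forward.
- Section 2.8: same technician and same equipment at both visits; lead not covered.
- Section 2.12: random intercept per participant and medication covariates; no lead term. The intercept absorbs a lead offset only if the offset is the same at both visits.

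So a switch is permitted, is not prevented elsewhere, and is not removed by the listed model.

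**Figures in the document.** The article states no SD, expected effect or power for QT or QTc, so there is no figure to reproduce. All inputs below are assumptions.

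**Effect on variance.** Write the observed change as the true change plus s·d. Here d is the between-lead QT difference and s is 0 without a switch, or +1 or −1 for a switch in either direction. If the switch directions balance and are unrelated to the true change, then

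proportional rise in variance = p × d² / SD²,

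where p is the proportion of participants switched, d the root-mean-square lead difference, and SD the standard deviation of the change without switching.

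| Case | p | d (ms) | SD (ms) | Rise in variance | Rise in SD |
|---|---|---|---|---|---|
| Low extreme | 0.10 | 5 | 20 | 0.1 × 25/400 = 0.6% | √1.00625 − 1 = 0.3% |
| Central, wider SD | 0.20 | 10 | 20 | 0.2 × 100/400 = 5.0% | √1.05 − 1 = 2.5% |
| Central, narrower SD | 0.20 | 10 | 15 | 0.2 × 100/225 = 8.9% | √1.0889 − 1 = 4.3% |
| High extreme | 0.30 | 15 | 15 | 0.3 × 225/225 = 30% | √1.30 − 1 = 14% |

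**Cross-check with a different parameterisation.** Suppose that V5 is the clearer lead with probability q, independently at each visit, and that the lead offset is a constant d. The switch probability is 2q(1 − q), the mean contribution to the change is zero, and the added variance is d² × 2q(1 − q).

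- q = 0.1, d = 10 ms: switch probability 0.18, added variance 18 ms². This is 18/400 = 4.5% with SD 20 ms and 18/225 = 8.0% with SD 15 ms, in line with the central cases above.
- Widest case, q = 0.5, d = 20 ms, SD 15 ms: 0.5 × 400/225 = 89%. This needs a coin-flip choice of lead at each visit and a larger offset than in the table.

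**QTc.** Bazett's formula divides QT by √RR, so the error carries over. At an illustrative RR of 0.8 s, a 10 ms offset becomes 10/√0.8 ≈ 11 ms.

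**Bias in the group contrast.** With a constant offset, the bias is r × d, where r is the difference between arms in the net switch rate (II to V5 minus V5 to II). If switching is unrelated to arm, r = 0 and the bias is 0. The article contains nothing from which a non-zero r could be derived.

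**The case against.** The strongest case against raising this has four parts.

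- **The article does not say that clarity is judged on each recording.** It could be judged once per participant. That is right, and the point is worded conditionally for that reason. The per-visit reading is the natural one, because clarity belongs to a tracing, but the text does not settle it.
- **Carrying the lead forward is reading-manual detail that a journal article leaves out.** This has some force. However, the article does state a lead rule and makes an explicit exception for QT, and that stated rule, followed literally, gives a worse measurement of change than a same-lead rule. It is a rule that can be improved, not just a missing detail.
- **A reader might infer that the lead rule contradicts section 2.8.** It does not. That section aims at variability between assessors and between instruments, and lead choice is neither. The two sections are compatible; section 2.8 simply does not cover the lead.
- **A reader might infer that the QT result will be biased, for example because training alters how clear each lead is.** The documents do not support this. They say nothing about training shifting lead clarity, the same rule applies in both arms, and assessment staff are described as blinded to group. Blinding does not strictly exclude bias if the intervention itself changed the tracings, but that remains an unquantified possibility.

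The assumed magnitude also spans about fifty-fold (0.6% to 30%), so it illustrates scale and does not show that the effect is material.

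**Conclusion.** The point holds as a minor improvement. The article permits QT to be read in different leads at baseline and week 12, and neither the consistency rule nor the listed model deals with that. If it happens, the lead difference enters the QT and QTc change. Under the stated assumptions the central cost is about 5–9% in variance, or about 2.5–4.3% in SD. For an individual switched participant, the recorded QT change is off by the whole lead difference.

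This rests on clarity being judged at each visit, on switch directions roughly balancing, and on assumed values for the lead difference, the switch rate and the SD of change. The outcome is one of many exploratory secondary measures. It would be wrong to conclude that the group comparison is biased, or that the trial's main inference is weakened: the co-primary outcomes (NMD and GWE) and the sample size do not depend on this measurement.

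**What to change.** Replace the QT lead rule with a same-lead rule. For each participant, measure QT in one lead at both visits, choosing between II and V5 whichever is adequately readable on both tracings. Make the choice blind to group and record the lead used. A stable lead offset then cancels from the within-participant change.

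The cost is about one sentence in section 2.11.8 or the ECG reading instructions and one extra data field. No additional recording is needed: a 12-lead tracing holds both leads, so ECGs already taken since recruitment began can be re-read, provided the tracings have been kept.

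The downside is that at one visit the lead used may be slightly less clear than the alternative, which trades a little reading error for the removal of switch error. For that reason the rule should ask for adequate readability on both tracings and not impose a fixed preference for lead II.

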#### 24-hour ambulatory electrocardiogram

2.11.9

The 24-hour ambulatory electrocardiogram (Holter) will be used to assess cardiac autonomic nervous function. Time-domain indices will include SDNN, RMSSD, and PNN50. Frequency-domain indices will include total power (TP), high-frequency power (HF), low-frequency power (LF), very low-frequency power (VLF), and the LF/HF ratio. Nonlinear indices such as SD1, SD2, and SDRR will also be analyzed to provide a comprehensive evaluation of autonomic modulation.

#### Arterial stiffness

2.11.10

Arterial stiffness and elasticity will be assessed using an arteriosclerosis detector (BP-203RPEIII, Omron, Japan) to measure brachial–ankle pulse wave velocity (baPWV) and the ankle–brachial index (ABI).

#### Vascular endothelial function

2.11.11

Flow-mediated dilation (FMD) will be evaluated using an ultrasound vascular imaging system (unexp18g, UNEX, Japan). FMD will be calculated using the formula:

$$\text{FMD\%}=\frac{\text{peak post-hyperemia diameter }-\text{ baseline arterial diameter}}{\text{baseline arterial diameter}}\times 100\%.$$

#### Blood pressure

2.11.12

Resting office systolic blood pressure (SBP), diastolic blood pressure (DBP), pulse pressure (PP), and rate–pressure product (RPP) will be measured using an automated sphygmomanometer (Omron HEM-3, Omron, Japan). Participants will be instructed to remain seated and relaxed during the measurement. Blood pressure will be measured three times, and the mean value of the last two readings will be used for analysis.

#### 24-hour ambulatory blood pressure

2.11.13

Dynamic blood pressure will be recorded using a noninvasive ambulatory blood pressure monitor (D2 Watch, Huawei, China). Daytime is defined as 06:00–22:00 and nighttime as 22:00–06:00. At least 90% of readings must be valid to ensure data reliability. The monitoring parameters include 24-hour mean SBP and DBP, daytime mean SBP and DBP, and nighttime mean SBP and DBP.

#### 24-hour movement behavior

2.11.14

24-hour movement behavior will be objectively monitored using a triaxial accelerometer (ActiGraph GT3X, USA) worn on the non-dominant wrist. The sampling frequency of the accelerometer will be set to 30 Hz with a recording epoch of 10 seconds. Participants will be instructed to maintain their usual daily routines (e.g., studying, household activities, and leisure activities) and wear the device continuously throughout the monitoring period.

#### Cardiopulmonary exercise testing

2.11.15

A graded incremental exercise test will be performed to measure participants’ peak oxygen uptake (VO_2peak_). Gas exchange will be analyzed using an indirect calorimeter (Cortex Meta Max 3B, CORTEX, Germany), and exercise load will be applied via a cycle ergometer (Monark 839E, Varberg, Sweden). Participants will perform a 3-minute warm-up at 50 W for men and 35 W for women. Thereafter, the workload will increase by 15 W per minute until the participant reaches volitional exhaustion. Gas analysis data will be collected every 10 seconds, and VO_2peak_ will be determined as the average oxygen uptake during the highest 30-second interval. Throughout the test, both subjective and objective fatigue levels will be monitored using the heart rate monitor Polar H7 (Polar Electro, Kempele, Finland) and the Borg Rating of Perceived Exertion (RPE) scale. Strict safety monitoring will be maintained throughout the test, and the specific criteria for immediate test termination are identical to those detailed in the ‘Safety considerations and adverse event monitoring’ section, adhering to ACSM guidelines. Achievement of VO_2peak_ will be confirmed when two or more of the following criteria are met: (1) a plateau in oxygen consumption despite increasing workload; (2) heart rate within ±10 beats per minute of the age-predicted maximum during the final stage; (3) respiratory exchange ratio (RER) > 1.1; and (4) RPE score ≥ 17.

#### Myocardial injury biomarkers

2.11.16

The serum levels of cardiac troponin I (cTnI), N-terminal pro-B-type natriuretic peptide (NT-proBNP), and creatine kinase-MB (CK-MB) will be determined using ELISA kits from Shenzhen Edan Instruments Co., Ltd. (m16). The specific experimental procedures will be carried out in strict accordance with the instructions provided with the kits.

#### Skeletal muscle injury biomarkers

2.11.17

The serum levels of creatine kinase (CK) and myoglobin (Myo) will be measured using ELISA kits from Shenzhen Edan Instruments Co., Ltd. (m16). The specific experimental procedures will be carried out in strict accordance with the instructions provided with the kits.

#### Circulating vascular function biomarkers

2.11.18

The serum levels of angiotensin-(1–7) [Ang-(1–7)], angiotensin II (Ang II), and endothelin-1 (ET-1) will be determined using ELISA kits from Jiangsu Enzyme Exemption Industry Co., Ltd. (MM-1719H2, MM-0004H2, and MM-0998H1, respectively). Serum nitric oxide (NO) levels will be measured by the microplate method using a kit from Jiangsu Edison Biotechnology Co., Ltd. (ADS-W-N005-96). The specific experimental procedures will be carried out in strict accordance with the instructions provided with the kits.

#### Circulating oxidative stress biomarkers

2.11.19

Serum reactive oxygen species (ROS) levels will be quantified using a green fluorescence method with a kit from Shanghai Beibo Biotechnology Co., Ltd. (Product No. BB-475015). Serum superoxide dismutase (SOD) and malondialdehyde (MDA) levels will be determined by the microplate method using kits from Jiangsu Edison Biotechnology Co., Ltd. (ADS-W-KY011 and ADS-W-YH002, respectively). Serum levels of nuclear factor erythroid 2-related factor 2 (Nrf2), Kelch-like ECH-associated protein 1 (KEAP1), heme oxygenase-1 (HO-1), glutathione peroxidase 4 (GPX4), and NAD(P)H quinone dehydrogenase 1 (NQO1) will be measured by ELISA using kits from Jiangsu Enzyme Exemption Industry Co., Ltd. (MM-2402H1, MM-50943H1, MM-1508H1, MM-60328H1, and MM-50945H1, respectively). The specific experimental procedures will be carried out in strict accordance with the instructions provided with the kits.

